### Sample characterization

Glycohemoglobin (HbA_1c),_ fasting plasma insulin level, fasting plasma glucose, plasma concentration of CRP, and lipid profile will be measured after 10 to 12 hours of fasting using the analyzer ADVIA 1800 Chemistry System (Siemens, Tarrytown, NY, USA). The degree of insulin resistance will be determined at baseline by the homeostasis model assessment of insulin resistance (HOMA-IR), according to the formula: HOMA-IR = fasting plasma insulin (μU/ml) x fasting plasma glucose (mmol/L)/22.5 [28]. Body composition will be evaluated by tetrapolar bioelectrical impedance analysis (model BC-558, Tanita Corporation of America Inc., Arlington Heights, IL, USA) which calculates body fat, total body water, muscle mass, visceral fat, and bone mass. The subjects will be required to avoid eating and drinking for 4 hours and to urinate prior to the assessment.

### Protocol

Following the screening session, the subjects will return to the laboratory on 5 different days (Fig. 2). They will be asked to avoid alcohol and caffeine and refrain from exercise for 24 hours before testing. All tests will take place in the morning, at the same time of the day.

**Fig. 2 Fig2:**
[figure not shown]
Experimental protocol flowchart. LEDT, light-emitting diode therapy

On the first day, incremental exercise on a cycloergometer (Quinton Corival 400, Seattle, WA, USA) will be performed to determine the gas exchange threshold (GET) and peak $$ p\overset{\cdotp }{V}{O}_2 $$. Subjects should maintain a cycling cadence of approximately 60 rpm. The workload increment will be determined for each subject in accordance with Wasserman et al. [29]. The GET will be determined by three independent observers according to the ventilatory method [29]. The peak $$ p\overset{\cdotp }{V}{O}_2 $$ will be the mean $$ p\overset{\cdotp }{V}{O}_2 $$ value of the last 30 seconds during the incremental exercise. It will be assumed that peak $$ p\overset{\cdotp }{V}{O}_2 $$ has been achieved when the respiratory exchange ratio (RER) at exercise peak reaches a value higher than 1.1 [30].

After that, the subjects will return to the laboratory four more times to receive the muscular pre-conditioning intervention (LEDT or placebo) according to the randomization. Immediately after the intervention, the subjects will perform moderate constant workload cycling exercise corresponding to 80 % of the $$ p\overset{\cdotp }{V}{O}_2 $$ during the GET. The LEDT will be administered with a multidiode cluster probe (50 GaAIA LEDs, 850 ηm, 75 mW each diode, and 3 J per point) before each exercise session. The probe will be in direct contact with skin bilaterally for 40 seconds, delivering 150 J of total energy to each quadriceps and triceps surae muscle. Placebo will follow the same procedure, but, the LEDT device will be turned off.

The constant workload exercise protocol will be preceded by a resting period and 3 minutes of freewheel pedaling. Afterwards, 6 minutes of exercise at target workload will be performed followed by a 6-minute cool-down period of freewheel pedaling.

### Measurements

The $$ p\overset{\cdotp }{V}{O}_2 $$, carbon dioxide output (*pVCO*_2_), minute ventilation (VE), and respiratory exchange rate (RER) will be measured breath-by-breath using a computerized metabolic cart (Vmax29c, Sensor Medics, Yorba Linda, CA, USA) previously calibrated for each session.

Electrocardiography (ECG) will be continuously recorded (CM5 lead) with a bioamplifier (BioAmp Power Lab, ADInstruments, Castle Hill, NSW, Australia) and a data acquisition system (Power Lab, ADInstruments, Castle Hill, NSW, Australia). Heart rate (HR) will be estimated based on the ECG signal. Finger arterial pressure will be measured using a photoplethysmography system (Finometer Pro, Finapres Medical System, Amsterdam, Netherlands). The finger cuff will be placed on the middle finger of the left hand. To correct the hydrostatic pressure changes related to the heart, a height correction will be used as recommended by the manufacturer [31].

Local tissue oxygenation of the vastus lateralis and gastrocnemius medialis of the right leg will be measured using near-infrared spectroscopy (NIRS) (Oxymon, Artinis Medical Systems, Nijmegen, Netherlands). NIRS provides measurements of changes in concentrations of deoxygenated and oxygenated hemoglobin (HHb and O_2_Hb, respectively). In addition, the tissue saturation index (TSI) will be measured. To avoid any motion artifact and ambient light influences, the probe will be fixed by tape and then a dark cloth will be gently wrapped around the thigh and calf region.

Before and after the constant workload exercise protocol, blood samples will be collected via earlobe puncture in order to verify lactate and glucose using an automated glucose analyzer (YSI 2300 STAT PLUS – Yellow Springs Instruments, Yellow Springs, OH, USA) that has been previously calibrated according to the manufacturer's instructions.

### Data analysis procedures

The $$ p\overset{\cdotp }{V}{O}_2 $$ and NIRS data collected during constant workload exercise will be submitted to time domain kinetics analysis as previously described [5, 32–34]. The data obtained in the two repetitions of the same constant workload protocol for each intervention (LEDT or placebo) will be time-aligned and second-by-second interpolated; then, the point-by-point mean between tests will be finally submitted to kinetics analysis.

### Statistical analysis

The data will be expressed as mean and standard deviation values. The Kolmogorov-Smirnov and Levene tests will be used to test the data for Gaussian distribution and variance, respectively. The statistics analysis will be performed using two-way repeated-measures ANOVA and a post hoc Tukey test for intergroup, intragroup, and multiple comparisons. The level of significance will be set at 5 % (p < 0.05). The statistical power will be set at 0.80, which is the minimal value recommended in the literature to minimize type II error.

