## Methods/Design

### Design

This study is a randomized, double-blind, placebo-controlled crossover trial approved by the Ethics Committee of Federal University of São Carlos (number 13573013.1.0000.5504) and registered at ClinicalTrials.gov under Trial Number NCT01889784. This study will be conducted in accordance with the human research standards set out by the National Health Council Resolution 196/96. The subjects will be included in the study after providing written informed consent.

The subjects will be divided into two groups: DM group (DMG) and healthy group (HG). After screening, the subjects of both groups who meet the eligibility criteria will be randomly allocated to one of two subgroups (A and B) as described in Fig. 1a. Four separate tests will be conducted to evaluate the acute effect of phototherapy. All subjects will receive both interventions, light-emitting diode therapy (LEDT) and placebo, with a minimum 14-day interval between sessions (washout period). The subgroups will determine the intervention order because the interventions will be alternated in each visit (Fig. 1b). The subjects in subgroup A will receive LEDT in the first and third sessions and placebo in the second and fourth sessions. Subjects in subgroup B will receive the reverse order. The researcher responsible for the randomization process will also prepare the LEDT device (effective or placebo) before each visit and will not analyze the data.

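### The stated two-way ANOVA leaves out the randomised sequence, so most visit-to-visit trends inflate the error of the LEDT comparison and, if subgroups A and B are unequal, bias it

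*Protocol article*

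**What the plan says.** The Design section describes a randomised crossover in which participants of both groups (diabetes, DMG, and healthy, HG) are allocated at random to subgroup A or B. "The subgroups will determine the intervention order because the interventions will be alternated in each visit". Specifically, "The subjects in subgroup A will receive LEDT in the first and third sessions and placebo in the second and fourth sessions", and "Subjects in subgroup B will receive the reverse order". Sessions are at least 14 days apart.

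Under Data analysis procedures, the two repetitions of each intervention are aligned and averaged for pulmonary oxygen uptake and NIRS, and "the point-by-point mean between tests will be finally submitted to kinetics analysis". Each participant therefore contributes one LEDT value and one placebo value for each kinetics parameter.

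Under Statistical analysis, "The statistics analysis will be performed using two-way repeated-measures ANOVA", followed by Tukey tests between groups, within groups and for multiple comparisons. The two factors are not named. Subgroup, visit, period and sequence do not appear in that section.

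**The concern.** Subgroup A or B is the only thing this trial randomises, and it fixes which visits supply the LEDT value and which the placebo value. In A, LEDT comes from visits 1 and 3 (mean 2) and placebo from visits 2 and 4 (mean 3). In B it is the other way round. Within any participant, one intervention is always one visit later on average.

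Four visits at least 14 days apart span at least 3 × 14 = 42 days, so familiarisation, training or glycaemic drift is possible. The washout deals with carryover and does nothing about such drift. A two-way model whose factors are group and intervention cannot separate drift from the LEDT effect or take it out of the error. LEDT against placebo is the trial's main question, so the precision of that comparison, and possibly its bias, is at stake.

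**Working it through.** **Figure in the plan.** The only design figure is power of 0.80. It cannot be reproduced, because no sample size, effect size or SD accompanies it.

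**How period enters.** Let p1 to p4 be the visit effects. Their contribution to LEDT minus placebo, after averaging the repeats, is
- A: (p1+p3)/2 − (p2+p4)/2
- B: the same with the opposite sign.

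For a linear trend of δ per visit (0, δ, 2δ, 3δ), A gets (0+2δ−δ−3δ)/2 = −δ and B gets +δ. For a shift c between the first visit and all later ones, A gets (0+c−c−c)/2 = −c/2. For a step c only between visits 2 and 3, A gets (0+c−0−c)/2 = 0. So the contribution vanishes only when p1+p3 = p2+p4.

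**Equal subgroups.** The shifts −δ and +δ cancel in the mean. They remain as spread between participants, so the variance of the difference is multiplied by about 1+δ², with δ in SDs of the paired difference: 1.06, 1.25 and 2.00 at δ = 0.25, 0.5 and 1.0.

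**Unequal subgroups.** The mean shift is (−δ·nA + δ·nB)/(nA+nB) = δ(nB−nA)/(nA+nB). For nA:nB = 8:4 this is −δ/3, that is −0.08, −0.17 and −0.33 SD. For 4:8 it has the opposite sign.

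**Power and type I error (simulated).** Assumptions: one group of 12, SD of the difference 1, effect 0.89 SD (80% power with no trend), two-sided 5%, linear trend. Unadjusted is the paired test. Adjusted takes the equal-weight mean of the two subgroup means.

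| Split A:B | δ | Bias (SD) | Type I error, unadjusted | Power, unadjusted | Power, adjusted |
|---|---|---|---|---|---|
| 6:6 | 0.25 | 0 | 4.4% | 78% | 79% |
| 6:6 | 0.5 | 0 | 3.0% | 72% | 79% |
| 6:6 | 1.0 | 0 | 0.7% | 49% | 79% |
| 8:4 | 0.25 / 0.5 / 1.0 | −0.08 / −0.17 / −0.33 | 5.0–5.7% | 70 / 54 / 17% | about 75% |
| 4:8 | 0.25 / 0.5 / 1.0 | +0.08 / +0.17 / +0.33 | 5.0–5.7% | 85 / 87 / 85% | about 75% |

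The adjusted test keeps a type I error of about 5% throughout. The higher unadjusted power at 4:8 comes from bias in the favourable direction, so it is no gain.

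**Sensitivity to n.** With 20 participants and an effect of 0.66 SD, an equal split gives unadjusted power of 78%, 72% and 50% at the same δ, against 80% adjusted. A 6:14 split gives bias of 0.10, 0.20 and 0.40 SD and unadjusted type I error of 6.4%, 9.7% and 16.5%.

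**Price of adjusting.** The adjusted estimate has variance (1/4)(1/nA+1/nB). At 6:6 this is 1/12, the same as unadjusted. At 8:4 it is (1/4)(1/8+1/4) = 0.094 against 1/12 = 0.083, a ratio of 1.125. With no trend, power goes from 80% to about 79% at 6:6 and to about 75% at 8:4.

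**The case against.** **The factors are inferred, and this is a condensed article.** That is true: a fuller analysis plan may exist. But the article names a specific model. If the listed between-group and within-group comparisons take its two factors, it has no room for sequence, so a fuller plan would have to change the model and not merely elaborate it.

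**The trends assumed may be too large.** δ is per visit, so δ = 1.0 means 3 SDs of drift over the four visits and δ = 0.25 means 0.75 SD. At δ = 0.25 and equal subgroups the loss is about one point of power. The Protocol section also limits drift: an earlier cycling test on day one, a fixed time of day, and 24 hours without exercise, alcohol or caffeine. This stands, and it is why the point is not urgent.

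**Stronger readings that the article does not support.** A reader might infer that any visit effect biases the LEDT result. It does not: some patterns cancel, and with equal subgroups there is no bias and the test is conservative, so omitting sequence does not raise the false-positive rate there. A reader might also infer that the allocation is unblocked and imbalance therefore likely. The article says only that allocation is random, and block details are commonly left out of an article, so that is no finding. Imbalance could still arise from dropout.

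**The simulation covers one group, not the two-group ANOVA.** This is fair. With 12 per group and 8:4 in both, type I error for the intervention main effect is about 6%, 8% and 12%. With 8:4 in one group and 4:8 in the other, the bias cancels in the main effect. It then moves to the group × intervention contrast, as −δ/3 − δ/3 = −2δ/3.

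**Conclusion.** The point holds as an advisable improvement. On the inferred reading of its factors, the stated model omits the randomised sequence, and averaging the repeats does not protect against this. With equal subgroups the consequence is lost precision: negligible at δ = 0.25, about 7 points of power at δ = 0.5 (72% against 79%), and large only for a strong trend. Bias in the LEDT effect needs both a trend that does not cancel and unequal subgroups, and it can go in either direction.

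The algebra rests only on the visit schedule in the Design section. Every magnitude rests on an assumed sample size, effect and trend, because the article gives none of them.

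**What to change.** **Averaged oxygen-uptake and NIRS kinetics.** Keep group, intervention and group × intervention, and add subgroup (A/B) and intervention × subgroup. After averaging, the interaction carries the odd-versus-even-visit period effect. Estimate the LEDT effect, overall and within DMG and HG, as the equal-weight mean over A and B. A model with visit as a factor cannot be fitted to these parameters as planned, because the curves are averaged before the kinetics fit and no per-visit parameters exist.

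**Outcomes analysed by visit.** Where values are kept by visit, as could be done for lactate and glucose, use a linear mixed model with group, intervention, group × intervention, subgroup and visit as fixed effects and a random participant effect.

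**Cost.** A few lines of analysis text and one or two error degrees of freedom. If there is no trend, about 1 point of power is lost at a 6:6 split and about 5 points at 8:4 (12 participants assumed). No extra visits or data are needed. The Trial status section says recruitment is under way, so the terms can be fixed in writing before the data are analysed.

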## Discussion

The chronic effect of phototherapy has been widely studied and shows promising results related to increased peak $$ p\overset{\cdotp }{V}{O}_2 $$, reduction in fatigue, and lactate and C-reactive protein concentrations [23, 24–26]. This novel therapeutic tool is generally studied in healthy participants [17, 18, 23, 25, 26]; however, the acute effects of phototherapy are still unknown in DM and its impact on $$ p\overset{\cdotp }{V}{O}_2 $$ dynamics still needs further clarification.

The effects of LEDT could be beneficial to the DM population because the exercise intolerance of this population decreases quality of life and further increases cardiovascular risk. Therefore, the purpose of this randomized clinical trial is to evaluate the acute effects of LEDT on $$ p\overset{\cdotp }{V}{O}_2 $$ dynamics in subjects with DM and healthy age- and sex-matched subjects. The results will elucidate the effects of LEDT and may support the use of this therapy in individuals with DM.

Data will be published after the study is completed.

### Trial status

Patient recruitment is currently underway.

## Abbreviations

BMI: body mass index
DM: Type 2 diabetes
DMG: Type 2 diabetes group
ECG: electrocardiogram
GET: gas exchange threshold
HbA_1c_: glycohemoglobin
HHb: deoxygenated hemoglobin
HG: healthy group
(HOMA-IR): homeostasis model assessment of insulin resistance
HR: heart rate
hs-CRP: high-sensitivity C-reactive protein
LED: light emitting diode
LEDT: light-emitting diode therapy
NIRS: near-infrared spectroscopy
O_2_: oxygen
O_2_Hb: oxygenated hemoglobin
pVCO_2_: carbon dioxide output
$$ \left(p\overset{\cdotp }{V}{O}_2\right) $$: pulmonary oxygen uptake
RER: respiratory exchange ratio
TSI: tissue saturation index
VE: minute ventilation
